#### Setting

Participants will be recruited from acute psychiatric inpatient wards within the catchment areas of three NHS mental health Trusts in England; one in inner London, one in outer London, and one covering a mixture of non-metropolitan areas in the North-West of England. Each Trust is the provider of a range of acute and community psychiatric services in its local catchment area. Both London Trusts have highly ethnically diverse catchment areas.

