### Allocation

Randomisation will take place following the completion of baseline measures. Researchers at UCL who are independent of the study will allocate participants via a computer-generated allocation sequence to either the intervention or control group in a 1:1 ratio using block randomisation stratified by site (3:3:2 ratio inner London: outer London: North-West England) and ethnicity (ethnic minority groups at higher risk of detention vs lower risk groups 1: 1 ratio).

Some of the study team will be unblinded so that they are able to deal with any issues with intervention delivery as they arise. Other members of the study team, such as the study research assistants who will be collecting follow-up outcomes, will be kept blind to treatment allocation as far as possible. The study team will liaise with the PMHWs, who will not be blinded, to minimise the likelihood that the blind researchers will be accidentally exposed to information about group allocation (known as ‘blind breaks’). Blinding will be monitored, and if any blind breaks occur, they will be systematically recorded.

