### Sample size

We aim to recruit 80 participants in line with recommendations by Consolidated Standards of Reporting Trials (CONSORT) for a pilot randomised controlled trials (RCTs) and to randomised them to either intervention or control group [28]. This is deemed a sufficient sample to examine the primary aim of the study, which is assessing feasibility parameters to inform decisions about a future fully-powered confirmatory trial—we have considered the need to have sufficient data both about the sample as a whole and high-risk ethnic groups.

The statistical power of the current feasibility trial will result in 80% power (with a two-sided alpha of 5%) of detecting a reduction in rates of compulsory readmission from 50 to 20% following the recruitment of 80 participants. Such a large difference between arms is not expected, but the risk of detention in each group will inform the calculation of sample size and can also inform a calculation of how likely it is that a significant result would be achieved in a full study (see Analysis section below).

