### Health economic analysis

Service use data will be collected using an adapted version of the Client Service Receipt Inventory (CSRI) [35]. Costs will be calculated by combining this information with appropriate unit costs. The costs of the intervention will be calculated from information on staff time and other requirements.

Descriptive data such as demographic and clinical/service user characteristics will also be recorded, including Community Treatment Order status, previous admission and compulsory detention history clinical diagnosis, and demographic data including age, sex, and ethnic group.

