### Inferential analyses

This pilot study will not have sufficient statistical power to assess the effectiveness of the intervention but will allow an assessment of whether the direction and magnitude of any effect found for the proposed primary outcome are consistent with a hypothesis that the programme is effective in reducing repeat detentions. For this reason and to test the analysis envisaged for a future, fully powered, effective RCT, primary outcome at follow will be compared between study arms, using appropriate multi-level models. Our planned analysis is hierarchical multi-level modelling, allowing for the clustering of residuals between centres by introducing the variable coding for centre as a random intercept. We will enter all other stratification variables as fixed effects. Other potential baseline covariates (e.g. age, ethnicity) will be entered in serial adjusted models where relative fit will be assessed using Akaike and Bayesian Information Criteria. The goodness of fit will be determined using Hosmer Lemeshow test of fit. We will assess the robustness of the results to missing data by carrying out sensitivity analyses in which the missing data are assigned extreme values to determine the effect of potential extreme missing values on the stability of the reported results. We will assess the effect of time by analysing results with time as a random slope variable.

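### The primary-outcome analysis includes a random slope for time that a single yes/no outcome cannot identify, and a random centre intercept that three centres estimate very poorly

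*Protocol article*

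**What the plan says.** All references are to the protocol article.

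- **Model.** Inferential analyses plans a hierarchical model for the primary outcome, "allowing for the clustering of residuals between centres by introducing the variable coding for centre as a random intercept". The remaining stratification variables enter as fixed effects.
- **Centres.** Setting names "acute psychiatric inpatient wards within the catchment areas of three NHS mental health Trusts in England". Participant eligibility criteria gives targets of 30, 30 and 20.
- **Allocation.** Randomisation is "in a 1:1 ratio using block randomisation stratified by site" and by ethnicity in two groups (higher or lower risk of detention).
- **Further covariates.** Age and ethnicity are given as examples of other baseline covariates, which "will be entered in serial adjusted models where relative fit will be assessed using Akaike and Bayesian Information Criteria".
- **Time.** The paragraph closes: "We will assess the effect of time by analysing results with time as a random slope variable". It names neither an outcome nor a grouping level for this slope.
- **Outcome.** Trial outcomes defines the primary outcome as whether the participant was detained within one year of randomisation, taken from health records. Detention within 24 months is a separate secondary outcome.
- **Status.** Inferential analyses says the pilot is not powered to assess effectiveness, and that the comparison is also run to try out the analysis intended for the full RCT.

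**The concern.** Two parts of the stated model ask for more than the design supplies. A random slope for time needs repeated measurements within some unit, and the outcome under discussion is recorded once. A random intercept for centre needs enough centres to estimate a variance, and there are three. When the estimated variance is zero, centre drops out of the model although randomisation was stratified by it.

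The risk is less a wrong pilot result than a failed rehearsal. An analyst who follows the text literally meets a term that cannot be fitted and, often, a boundary estimate. Neither outcome tells the team whether a random-centre model would work in the full trial. The second listing of ethnicity also leaves unclear which terms belong to the base model.

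**Working it through.** **1. The plan's own figure.** Sample size claims "80% power (with a two-sided alpha of 5%) of detecting a reduction in rates of compulsory readmission from 50 to 20" per cent with 80 participants, so 40 per arm. Using z = [Δ√n − 1.96·√(2p̄(1−p̄))] / √(p₁(1−p₁)+p₂(1−p₂)), with Δ = 0.30 and p̄ = 0.35:

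z = (0.30·√40 − 1.96·√0.455) / √(0.25+0.16) = (1.897 − 1.322) / 0.640 = 0.898, which gives 81.6% power.

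The 80% claim reproduces as a plain two-proportion test with no dropout. It does not depend on the multilevel model.

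**2. Time slope on the 12-month outcome.** There is one row per participant and a common time t. If the slope sits at centre level, the centre contribution is b₀ + b₁t, with variance σ₀² + 2tσ₀₁ + t²σ₁². With t constant, only that sum enters the likelihood, so σ₁² cannot be separated from σ₀². If the slope sits at participant level, there is one binary value per unit and nothing from which to estimate a within-person slope.

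**3. Stacking the 12- and 24-month outcomes.** The later outcome contains the earlier, so each person shows 00, 01 or 11, and 10 is impossible. Three cells give two free probabilities per covariate pattern. A participant-level intercept-and-slope model needs an intercept, a time effect, two variances and a covariance, which is five parameters. It would also give positive probability to the impossible pattern. At centre level, two variances and a covariance would rest on three units.

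**4. Random intercept on three centres.** Random-intercept logistic models were fitted by maximum likelihood (Gauss-Hermite quadrature), with centres of 30, 30 and 20. The assumed rates are 43% and 28%, the 24-month figures that Background quotes from the Zürich trial: ln(0.28/0.72) − ln(0.43/0.57) = −0.66. Three separate simulations gave these shares of trials with an estimated centre SD of about zero:

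| True SD (log-odds) | Run A (300 trials) | Run B (300 trials) | Run C (400 trials) |
|---|---|---|---|
| 0 | 81% | 74% | – |
| 0.3 | 63% | 65% | 60% |
| 0.5 | 45% | 46% | 47% |
| 1.0 | – | 24% | – |

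Runs A and C also assumed an ethnicity log odds ratio of 0.5; run B assumed none. Monte Carlo error is about 3 points (√(0.65·0.35/300) = 0.028). In run B, at a true SD of 0.5, the 5th to 95th percentile range of the estimated SD was 0 to 1.17.

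**5. Effect on the treatment estimate.** Run C balanced allocation within each site-by-ethnicity stratum and compared the random-intercept fit with fixed centre terms. Where the variance collapsed, the arm log odds ratio differed by a median of 0.01 (95th percentile 0.05, maximum 0.10), against a standard error of about 0.50. Significance at 5% changed in at most about 1% of those fits. Across all fits the median difference was 0.02.

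**6. Can fixed centre terms be afforded?** The terms are arm, ethnicity stratum and two centre indicators: four parameters. On the protocol's own rates, 40·0.5 + 40·0.2 = 28 events are expected, or 28/4 = 7 per parameter. All 500 simulated datasets analysed with fixed centre terms could be fitted.

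**7. Ethnicity.** Allocation makes it a stratification factor, so the fixed-effects sentence already includes it. The next sentence offers it again as an optional covariate.

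**The case against.** The strongest reply is that fixed versus random centre makes almost no difference here. Step 5 bears this out: stratified 1:1 allocation makes arm nearly independent of centre, and a zero variance is a legitimate maximum-likelihood result. The full trial may also have more centres. What remains is that three centres say nothing useful about how a random-centre model would behave there.

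The time-slope sentence does not name its outcome and could be meant for the interview measures at baseline, 6 and 12 months. That is possible, but it stands in a paragraph about the primary outcome, and the only grouping level named there is centre.

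Ethnicity as a covariate might mean a finer coding than the two-level stratum. If so, the text should say that, because a finer coding nested in the stratum makes the stratum term redundant.

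Several stronger readings are tempting and are not supported:

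- **That the centre intercept cannot be estimated at all.** It can be fitted; it is estimated very imprecisely. Only the time slope is unidentifiable.
- **That covariates are picked by AIC or BIC.** The text says only that relative fit will be assessed, not that the best-fitting model is the one reported.
- **That the plan yields no single treatment effect.** The planned analysis defines a base model with one arm effect. Which model carries the primary label, and the full covariate list, may properly sit in the separate analysis plan promised under Statistical analysis.
- **That leaving detention history unnamed is an error.** The protocol records "previous admission and compulsory detention history clinical diagnosis", and the covariates named are only examples.
- **That the Hosmer-Lemeshow test sees at most 12 covariate patterns.** That count (2 × 2 × 3) holds for the base model only; adding age gives many more.

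**Conclusion.** The point holds in limited form. A random slope for time is not identifiable for the 12-month binary outcome, and the 24-month outcome does not repair this. That follows from the outcome definition and needs no assumption beyond reading the sentence as applying to the outcome its paragraph discusses.

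The centre variance is very poorly estimated from three Trusts, at about zero in 60 to 65% of trials at a true SD of 0.3 and 45 to 47% at 0.5. These shares rest on the Zürich rates and the assumed SDs, since the protocol gives no between-centre variation. The consequence for the treatment estimate is small.

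The double listing of ethnicity is a plain inconsistency unless a finer coding is intended.

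Severity is minor to moderate. The comparison is declared non-confirmatory, no item under Progression criteria depends on this model, and the 80% power statement is untouched. The point still merits correction before unblinding, because this analysis is being tried out for the full trial.

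**What to change.** 1. Delete the random time slope for the primary outcome. If time is of interest, analyse time to first new detention from the record dates, defining the start of risk because participants are inpatients when randomised. Alternatively, state that the slope applies only to the repeated interview measures, with participant as the grouping level. In that case baseline must be one of the occasions. For a continuous score, three occasions supply six variance and covariance terms for four parameters (two random-effect variances, their covariance and a residual variance). Two occasions supply only three.
2. Enter centre as two fixed indicator terms, with arm and ethnicity stratum. The choice for the full trial can be made once its number of centres is known.
3. Remove ethnicity from the optional covariates, or say which finer coding is meant and how it relates to the stratum.
4. Report this base model as primary, with the serially adjusted models and their AIC and BIC as supportive. The label has some practical value. In a simulation with four assumed covariates, two of them prognostic, p<0.05 switched between models of the series in 11% of runs.

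The cost is a change of wording, plus two parameters for centre in place of one variance. Sample size and data collection stay as they are, provided detention dates are extracted if the time-to-event option is taken.

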### Missing data

Patterns of missingness in recorded data will be reported as part of the feasibility outcome of the ability to retain participants in the study. Reasons for missingness will be investigated and reported We will conduct threshold analyses to describe the extent to which any missing data could make a qualitative difference to the result by imputing a poor outcome for all intervention group missing subjects, and an average one for all control group missing subjects, and vice versa. We will report the outcome of these statistical investigations where appropriate.

### Health economic analysis

Service use data will be described in each arm to inform future analysis. QALYs will be derived from measures of quality of life and correlations between these, and other outcomes will be calculated. This will inform the choice of QALY measures for a future trial.

## Monitoring for adverse events

Both groups will be monitored for the occurrence of adverse events (AEs) and a log kept. The severity of adverse events is assessed by several categories, where severe adverse events are those that result in alteration, discomfort, or disability which is clearly damaging to health. All serious adverse events (SAEs) will recorded in a trial log and assessed by the chief investigator (CI) and site principal investigators as likely to be related to the intervention (a causal relationship between the intervention and an adverse event is at least a reasonable possibility, i.e. the relationship cannot be ruled out); not related (there is no reasonable possibility of a causal relationship between the intervention and an adverse event); not assessable (unable to assess on information available).

All serious AEs will be recorded in the medical records, the CRF, and the sponsor’s AE log. The log of SAEs will be reported to the sponsor twice per year. Where the event is unexpected and thought to be related to the intervention, this will be reported by the Investigator to the Health Research Authority within 15 days. Completed SAE forms must be sent within 5 working days of becoming aware of the event to the Sponsor (the UCLH/UCL Joint Research Office, acting on behalf of UCL).

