**Method:**

We have adapted and manualised an intervention previously trialled in Zürich Switzerland, aimed at reducing future compulsory detentions among people being discharged following a psychiatric admission that has included a period of compulsory detention. A co-production group including people with relevant lived and clinical experience has co-designed the adaptations to the intervention, drawing on evidence on crisis planning and self-management and on qualitative interviews with service users and clinicians. We will conduct a randomised controlled feasibility trial of the intervention, randomising 80 participants to either the intervention in addition to usual care, or usual care only. Feasibility and acceptability of the intervention and trial procedures will be assessed through process evaluation (including rates of randomisation, recruitment, and retention) and qualitative interviews. We will also assess and report on planned trial outcomes. The planned primary outcome for a full trial is repeat compulsory detention within one year of randomisation, and secondary outcomes include compulsory detention within 2 years, and symptoms, service satisfaction, self-rated recovery, self-management confidence, and service engagement. A health economic evaluation is also included.

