### Discontinuation/withdrawal of participants

When consenting to participate in the trial, participants are consenting to randomisation, assessments, intervention, follow-up, and data collection. Participants also consent to the research team continuing to collect data from medical records should they lose capacity at any point during the trial, unless this consent is withdrawn. A participant who is known to lack capacity at the time of a follow-up interview will not be contacted for further assessments, but data collected up to that point will be retained, and the team will continue to use data from the participant’s medical records unless a request to withdraw from the use of this data is received, in which case no further data will be collected. If a participant who has lost capacity regains it within the timeframe for interview assessments, they will be contacted to seek consent to carry these assessments out (this maximises the numbers who can be included despite the transient loss of capacity which is frequent among people with severe mental health problems).

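### SAE relatedness and the 15-day report are tied to the intervention alone, so an unexpected SAE due solely to a research interview is coded not related and is not expedited

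*Protocol article*

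**What the plan says.** The section Monitoring for adverse events covers both arms: "Both groups will be monitored for the occurrence of adverse events". The chief investigator and the site principal investigators place each SAE in one of three categories:

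- *Related*: "a causal relationship between the intervention and an adverse event is at least a reasonable possibility", which the section explains as a link that cannot be excluded.
- *Not related*: "not related (there is no reasonable possibility of a causal relationship between the intervention and an adverse event").
- *Not assessable*: "not assessable (unable to assess on information available").

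The report to the Health Research Authority within 15 days has two conditions: "Where the event is unexpected and thought to be related to the intervention". Separately, every SAE is recorded in the trial log, the medical records, the case report form and the sponsor's log. A completed form goes to the sponsor within 5 working days, and no relatedness condition is attached to that step.

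Other sections show what participants are exposed to. Interventions describes the study intervention as four initial sessions followed by monthly contacts, and offers controls usual care only. Trial outcomes schedules research interviews for all participants at baseline, 6 and 12 months. Discontinuation/withdrawal of participants lists assessments and intervention as separate things agreed to: "participants are consenting to randomisation, assessments, intervention, follow-up, and data collection".

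**The concern.** Taking part in this trial means two exposures: the intervention, in one arm, and the research procedures, in both. The relatedness scheme asks about the first only. It is also closed, so an event caused by the second has to go into a category written for something else.

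Two things are at stake. The first is a correct record of whether the research interviews did harm. The second is prompt notice to the Health Research Authority when such harm is unexpected. Both matter somewhat more here than in most small trials, because the procedures are themselves under test. The abstract says: "Feasibility and acceptability of the intervention and trial procedures will be assessed through process evaluation". The Discussion likewise makes the working of the trial processes part of the main goal, and acknowledges that the participants may be acutely unwell and mistrustful of services.

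**Working it through.** There is no figure to reproduce. The check is to apply the written definitions to each kind of case.

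**Inputs** (all from the protocol article)

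1. *Related*, *not related* and the 15-day trigger each name the intervention and nothing else (Monitoring for adverse events).
2. *Not assessable* is for lack of information only (same section).
3. The intervention is the sessions and monthly contacts, offered to one arm (Interventions).
4. Research interviews are held in both arms (Trial outcomes), and assessments are distinct from the intervention (Discontinuation/withdrawal of participants).
5. No other section extends relatedness or the 15-day report to trial procedures.

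**Applying the rule to an unexpected SAE**

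| Case | Code as written | 15-day report | Form to sponsor |
|---|---|---|---|
| Either arm: cause unclear, too little information | Not assessable | Not triggered | Within 5 working days |
| Intervention arm: link to the intervention cannot be ruled out | Related | Yes | Within 5 working days |
| Intervention arm: attributed solely to a research interview | Not related | No | Within 5 working days |
| Control arm: attributed solely to a research interview | Not related | No | Within 5 working days |

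The last two rows are the defect. The assessor has a cause in view, so *not assessable* does not apply. That cause is not the intervention, so *related* does not apply. *Not related* is all that remains, and it takes the event outside the 15-day rule.

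**Why the control arm is affected most.** In the intervention arm the threshold for *related* is low: it is enough that a link cannot be ruled out. Some events that follow a follow-up interview will therefore be coded *related* anyway. A control participant has not been offered the intervention, so unless there is contamination that route is closed.

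**What the definitions do not touch.** Feasibility outcomes plans SAE rates in each arm. Those rates count SAEs whatever their relatedness, so the code does not enter them.

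**The case against.** The strongest reply is that little is lost in practice. An interview-linked SAE is still recorded in several places and still goes to the sponsor within 5 working days, sooner than the 15-day report. The steering committee also oversees safety. This stands, and it limits the point to the code and the report to the Health Research Authority.

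A second reply is that the control-arm result is close to a truism: people who were not given the intervention cannot be harmed by it. That is fair if relatedness is meant only as attribution to the intervention. It does not answer the point, because the same code also decides which events are expedited, and control participants undergo the trial's interviews.

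A third reply is that the acceptability of procedures is judged through recruitment, retention, completion rates and qualitative interviews, not through SAE coding. This too stands. The narrow code does not defeat that aim; it leaves out one piece of evidence relevant to it.

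A fourth reply is that an article condenses a fuller protocol, and the SAE form is not shown. That would excuse silence, but the article states the definitions and the trigger. If the full protocol is wider, the article should be brought into line with it.

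Qualitative interviews and session recordings would be weak examples. The former explore experiences of the intervention and the latter record its sessions, so a link to the intervention often could not be ruled out. The point therefore rests on the research interviews.

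**Conclusion.** The point holds in a narrow form. As written, an unexpected SAE attributable solely to a research interview is coded *not related* and does not trigger the 15-day report, and barring contamination no control-arm SAE can be coded *related*. This follows from a stated rule, not from a missing detail.

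Its size cannot be put as a number of events. The documents give no rate of SAEs due to interviews, and such events may be rare or absent. A reader might multiply participants by interviews to suggest a scale, but that counts contacts, not harms, and assumes that every interview takes place.

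Two stronger readings are tempting and are not supported. One is that these events vanish from safety reporting; the logging rules and the sponsor form show that they do not. The other is that the trial's results by arm are distorted; the plan promises SAE rates by arm, not relatedness by arm.

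The conclusion assumes that the intervention means the sessions and contacts described under Interventions, and that no document outside the article already widens the definitions.

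**What to change.** In Monitoring for adverse events and on the SAE form, change three places: the definition of *related*, the definition of *not related*, and the trigger for the 15-day report. In each, replace the reference to the intervention with *the intervention or any trial procedure (such as research interviews)*, and state that it applies in both arms. Add one field to the SAE form to record which of the two is suspected, so that attribution to the intervention can still be read off separately.

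The cost is a wording change and one form field, with no extra participants or visits. The downside is that a few more events may need expedited reporting.
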